**Figure 1 F1:**
[figure not shown]
**Schematic representation of the study procedure**.

### Study endpoints

Primary endpoints include (i_i_) patient-centered outcomes (i.e., anxiety, depression, ICD acceptance, QoL); (i_ii_) health care utilization; and (i_iii_) cost-effectiveness of the intervention. Secondary endpoints include (ii_i_) cortisol awakening response; and (ii_ii_) ventricular arrhythmias.

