### Study procedure, randomization and follow-up

The study protocol will be approved by the medical ethics committees of the participating centers. The study will be conducted according to the Declaration of Helsinki, as amended in 2008 by the World Medical Association, and all patients will be informed orally and in writing about the purpose, rights, and possible benefits/risks of the study.

Patients will be invited to participate in the study while hospitalized for their ICD implantation. Patients responding positively to the invitation will be given the informed consent form and the baseline questionnaire package. In order to avoid measuring pre-operative stress, patients will be asked to complete the baseline assessment between 5 and 10 days (T_0_) after implantation. If the baseline questionnaire is not returned within 7 days, patients will receive a reminder telephone call. When the signed informed consent form and completed baseline assessments are received at the trial coordinating center, the coordinating center will randomize the patient either to the treatment arm or to usual care. There will be a separate randomization list for each participating hospital. The patient will be informed by telephone to which condition he/she has been randomized and the procedure for the rest of the study. If the patient is randomized to the internet intervention, he/she will receive a login and password in order to be able to access the intervention. The day of randomization will be the first day of the intervention period, with the duration of the intervention being 12 weeks. For both study conditions, the follow-up assessments will take place 14 (T_1_), 26 (T_2_), and 52 weeks (T_3_) post implantation. All randomized patients, irrespective of condition, will be followed until the scheduled study end. A schematic representation of the study design is shown in Figure 1.

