#### Assessment of primary endpoints

All primary endpoints in addition to psychological factors, such as Type D personality [29], will be assessed with standardized and validated measures shown to have acceptable psychometric properties (Table 1). Disease-specific measures include the Florida Shock Anxiety Scale [30], the Minnesota Living with Heart Failure questionnaire [31], the ICD Patient Concerns questionnaire [16], and the Florida Patient Acceptance Survey [32,33].

**Table 1 T1:** Patient-centered outcomes and psychological factors assessed in the trial

Construct	Questionnaire		T_0_	T_1_	T_2_	T_3_
Anxiety	STAI-S	State Trait Anxiety Inventory (state only)	**x**	**x**	**x**	**x**
	FSAS	Florida Shock Anxiety Scale	**x**	**x**	**x**	**x**
	PDS	Posttraumatic Stress Scale		**x**	**x**	**x**
	DAI-4	Denollet Anxiety Inventory	**x**	**x**	**x**	**x**
Depressive symptoms	HADS	Hospital Anxiety and Depression Scale	**x**	**x**	**x**	**x**
	PHQ-9	Patient Health Questionnaire	**x**	**x**	**x**	**x**
Quality of life	SF-12	Short Form Health Survey 12	**x**	**x**	**x**	**x**
	MLWFQ	Minnesota Living With Heart Failure Questionnaire	**x**	**x**	**x**	**x**
ICD concerns	ICDC	ICD Patient Concerns Questionnaire	**x**	**x**	**x**	**x**
ICD acceptance	FPAS	Florida Patient Acceptance Survey	**x**	**x**	**x**	**x**
Health care utilization and cost-effectiveness	TiC-P	Trimbos/iMTA questionnaire for Costs associated with Psychiatric Illness	**x**			**x**
Type D personality	DS14	Type D Scale	**x**	**x**	**x**	**x**

**T**_0 _= Baseline; **T**_1 _= 14 weeks; **T**_2 _= 26 weeks; **T**_3 _= 52 weeks.

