### Statistical analysis and power calculation

The trial is designed to show whether a web-based behavioral intervention is effective in improving patient-centered outcomes compared to usual care. The power analysis was performed in relation to anxiety as the primary endpoint, since anxiety is a pertinent outcome measure in ICD patients due to the unique feature of the ICD being able to provide a shock. With (i) an expected between group effect size of .30., based on a recent meta-analysis of web-based intervention for symptoms of anxiety and depression [36] and taking into consideration that our population consists partly of patients with subclinical anxiety and depression levels; (ii) alpha = 0.05; (iii) power = 0.80 (two-sided test), 350 patients are needed (i.e., 175 in each condition). Although we had a response rate of 82% in an earlier study [16,19], based on a more conservative response rate of 50%, 700 patients need to be approached.

The effectiveness of the intervention will be examined using the intention-to-treat principle, with the inclusion of all randomized participants in the statistical analysis regardless of whether they completed the intervention or the follow-up measurements. Missing data will be imputed using regression imputation techniques. Univariable and multivariable regression analyses (both linear and Cox proportional hazard regression analysis) and analysis of variance and analysis of covariance with repeated measures will be used to investigate the effect of the intervention on the endpoints. The type of regression analysis will depend on the endpoint in question. Demographic, clinical and psychological variables will be included in multivariable analyses in order to control for their potential confounding effects. A p-value < 0.05 will be used to indicate statistical significance. All data will be analyzed using SPSS 17.0 for Windows (SPSS Inc., Chicago, Illinois).

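### Six unranked primary domains are declared, but the trial is sized for a single anxiety test whose scale and time point are never named

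*Protocol article*

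**What the plan says.** The section on study endpoints states: "Primary endpoints include (i_i_) patient-centered outcomes (i.e., anxiety, depression, ICD acceptance, QoL); (i_ii_) health care utilization; and (i_iii_) cost-effectiveness of the intervention". The abstract gives the same list. Neither ranks the six domains.

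The section on assessment of primary endpoints links them to Table 1: "All primary endpoints in addition to psychological factors, such as Type D personality [29], will be assessed with standardized and validated measures". For the domains in that list, the table has four anxiety scales (STAI-S, FSAS, PDS, DAI-4), two for depressive symptoms (HADS, PHQ-9), two for quality of life (SF-12, MLWFQ) and one for acceptance (FPAS). The TiC-P serves both utilization and cost-effectiveness. On timing: "the follow-up assessments will take place 14 (T_1_), 26 (T_2_), and 52 weeks (T_3_) post implantation". All nine patient-reported scales are collected at each of these visits, and all except the PDS also at baseline.

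The section on statistical analysis and power narrows the target: "The power analysis was performed in relation to anxiety as the primary endpoint". It assumes "an expected between group effect size of .30., based on a recent meta-analysis of web-based intervention for symptoms of anxiety and depression", with two-sided alpha 0.05 and power 0.80, and arrives at 350 patients. For inference it gives one criterion: "A p-value < 0.05 will be used to indicate statistical significance". It offers linear and Cox regression and repeated-measures ANOVA and ANCOVA, with the regression type depending on the endpoint.

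**The concern.** The two sections disagree on what is primary. One gives six domains of equal standing, and the other gives anxiety alone. An analysis plan can add detail to either statement but cannot make both true.

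Narrowing to anxiety does not identify a test either. The power paragraph points in two directions. Its reason for choosing anxiety is that the device can deliver a shock, which suggests the shock-specific scale (FSAS). Its effect size comes from web interventions for anxiety and depression symptoms in general, which suggests a general scale such as the STAI-S. The PDS has no baseline, so the four scales cannot all be analysed with the same baseline adjustment.

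At stake is what a positive result would mean. If several measures count as primary and each is judged at 0.05, a nominally significant result on one of them can be presented as a primary finding with a false-positive risk well above 5%. The stated power would also attach to a comparison that could be chosen after the data are seen.

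**Working it through.** **Inputs from the article.** Standardised effect d = 0.30, two-sided alpha 0.05, power 0.80, 175 per arm (power paragraph). Four anxiety scales, and 4 + 2 + 2 + 1 = 9 patient-reported scales for the listed domains (Table 1). The article gives no correlations between measures, so these are assumed and varied.

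**1. Reproducing the stated sample size.** Per arm, n = 2(z₀.₉₇₅ + z₀.₈₀)² / d² = 2(1.960 + 0.842)² / 0.30² = 174.4, rounded up to 175, or 350 in total. Power at 175 per arm is Φ(d√(n/2) − 1.960) = Φ(0.30 × √87.5 − 1.960) = Φ(2.806 − 1.960) = 0.801. A t-test calculation gives 175.4 per arm and power 0.799. A one-sided test would need only 138 per arm. The figure is therefore correct, and it is the size for exactly one two-sided test at 0.05.

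**2. False-positive risk with one test per scale, each at 0.05.** For k independent tests the risk is 1 − 0.95^k. For k tests with common correlation r, it is 1 − E[P(|√r·C + √(1−r)·e| < 1.960 given C)^k], where C and e are independent standard normal and the expectation is over C.

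| Assumed r | 4 anxiety scales | 9 patient-reported scales |
|---|---|---|
| 0 | 18.5% | 37.0% |
| 0.3 | 17.4% | 32.6% |
| 0.5 | 15.6% | 26.9% |
| 0.7 | 13.0% | 20.2% |
| 0.8 | 11.4% | 16.6% |

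This gives about 11–19% for four scales (r from 0.8 to 0) and about 17–33% for nine (r from 0.8 to 0.3). Even the lowest entry is more than twice 5%.

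**3. Cost of keeping the four anxiety scales co-primary.** Bonferroni gives alpha = 0.05/4 = 0.0125, with critical value 2.498. Power for any one scale at 175 per arm is Φ(2.806 − 2.498) = 0.62. Restoring 0.80 needs 2(2.498 + 0.842)² / 0.30² = 247.8, so 248 per arm or 496 in total.

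**The case against.** The strongest reply is that this is a condensed article. Multiplicity control and the exact primary contrast are often left to the full protocol or the analysis plan, and neither is shown. The power paragraph also singles out anxiety and gives a reason, so the confirmatory question is narrower than the endpoint list suggests. Part of this stands. A reader might infer that the trial has no controlled error rate. The article supports only that it states none. The contradiction over what is primary remains, because both statements are in the text.

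A reader might also count tests by visit: 4 scales × 3 visits = 12, or 9 × 3 = 27. The false-positive risk would then be higher; for 12 tests it is about 19–40% at common correlation 0.8 down to 0.3. But the article plans repeated-measures analyses, which can give one treatment test per scale. Separate tests per visit are possible but not stated, so the conclusion does not rest on them.

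Nor does the article say that one significant scale makes the trial positive. It gives a significance threshold, not a success rule. The percentages above show what follows if the threshold is applied to each measure without ranking.

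The number of primary measures depends on reading. The endpoint list gives nine scales plus the TiC-P, which is ten instruments. The device-concerns questionnaire appears under primary assessment ("the ICD Patient Concerns questionnaire [16], and the Florida Patient Acceptance Survey [32,33") and in the stated aim, but not in the endpoint list. Cost-effectiveness may not be judged by a p-value at all. The four-scale result depends on none of this.

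**Conclusion.** The concern holds. The article declares six unranked primary domains in one place and one primary endpoint in another, and the powered test is not identified among four anxiety scales and three follow-ups. The sample-size arithmetic is right, but its 5% and 80% describe a comparison that the document does not name.

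The inflation in false-positive risk rests on three assumptions: one test per scale, each at 0.05; equal correlation between test statistics; and no effect on any scale tested. The four-scale range is the firmer of the two, because it accepts the article's own narrowing to anxiety.

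It might be tempting to conclude that a particular scale and visit, such as the STAI-S at week 14, is what the 350 patients were sized for. The document does not support this: the calculation fits any single comparison with d = 0.30.

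**What to change.** Before outcome data are seen, name one anxiety scale and either one time point or one repeated-measures treatment contrast as the single primary test at two-sided 0.05. The STAI-S at T1 is one example, since that scale has a baseline. If T1 is chosen to represent the end of the intervention, the two statements of when the 12 weeks start (the day of randomization, or 2 weeks after implantation) must first be reconciled.

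Make all other scales and times, utilization and cost-effectiveness secondary. Test them in a fixed order or with Holm adjustment, or report them as estimates with confidence intervals. Align the abstract, the endpoint section and the power paragraph.

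The cost is amendment wording. N = 350 stays valid, and no visits or questionnaires change. The downside is that the other outcomes can no longer be claimed as primary results.

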#### Assessment of primary endpoints

All primary endpoints in addition to psychological factors, such as Type D personality [29], will be assessed with standardized and validated measures shown to have acceptable psychometric properties (Table 1). Disease-specific measures include the Florida Shock Anxiety Scale [30], the Minnesota Living with Heart Failure questionnaire [31], the ICD Patient Concerns questionnaire [16], and the Florida Patient Acceptance Survey [32,33].

**Table 1 T1:** Patient-centered outcomes and psychological factors assessed in the trial

Construct	Questionnaire		T_0_	T_1_	T_2_	T_3_
Anxiety	STAI-S	State Trait Anxiety Inventory (state only)	**x**	**x**	**x**	**x**
	FSAS	Florida Shock Anxiety Scale	**x**	**x**	**x**	**x**
	PDS	Posttraumatic Stress Scale		**x**	**x**	**x**
	DAI-4	Denollet Anxiety Inventory	**x**	**x**	**x**	**x**
Depressive symptoms	HADS	Hospital Anxiety and Depression Scale	**x**	**x**	**x**	**x**
	PHQ-9	Patient Health Questionnaire	**x**	**x**	**x**	**x**
Quality of life	SF-12	Short Form Health Survey 12	**x**	**x**	**x**	**x**
	MLWFQ	Minnesota Living With Heart Failure Questionnaire	**x**	**x**	**x**	**x**
ICD concerns	ICDC	ICD Patient Concerns Questionnaire	**x**	**x**	**x**	**x**
ICD acceptance	FPAS	Florida Patient Acceptance Survey	**x**	**x**	**x**	**x**
Health care utilization and cost-effectiveness	TiC-P	Trimbos/iMTA questionnaire for Costs associated with Psychiatric Illness	**x**			**x**
Type D personality	DS14	Type D Scale	**x**	**x**	**x**	**x**

**T**_0 _= Baseline; **T**_1 _= 14 weeks; **T**_2 _= 26 weeks; **T**_3 _= 52 weeks.

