**Methods:**

WEBCARE is a multi-center, multi-disciplinary, randomized, controlled behavioral intervention trial designed to examine the effectiveness of a web-based approach in terms of reducing levels of anxiety and device concerns and enhancing QoL. Consecutive patients hospitalized for the implantation of an ICD will be approached for study participation while in hospital and randomized to the intervention arm (n = 175) versus usual care (n = 175) at baseline (5-10 days post implantation). Patients will complete assessments of patient-centered outcomes at baseline, 14, 26, and 52 weeks after implantation. Patients randomized to the intervention arm will receive a 12-week web-based behavioral intervention starting 2 weeks after implantation. Primary endpoints include (i_i_) patient-centered outcomes (i.e., anxiety, depression, ICD acceptance, QoL); (i_ii_) health care utilization; and (i_iii_) cost-effectiveness. All primary endpoints will be assessed with standardized and validated disease-specific or generic questionnaires. Secondary endpoints include (ii_i_) cortisol awakening response; and (ii_ii_) ventricular arrhythmias.

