### Intervention versus usual care

Patients randomized to the treatment arm will receive an internet-based intervention starting 2 weeks after implantation. They will receive a username and password to access the intervention via the web. Every week an automated email will be sent to the participants to explain the contents and exercises for the coming week. All the information, as well as the exercise forms, will be downloadable from the website in case participants prefer to read the information on paper. Master's level psychology students, trained and supervised by psychologists will provide feedback on the completed exercises. This feedback is not meant to be therapeutic; it will be directed toward mastering the problem-solving strategies. The maximum amount of time the psychology students should spend on feedback will be 60 minutes per participant. The components of the intervention are presented in Table 2. The intervention has to be completed within 12 weeks, as we learnt in an earlier trial that one session a week is too fast a pace for most people. A typical session takes about 30 minutes and consists of an introduction, a discussion of the previous lesson's homework, new theory and homework for the subsequent week. The sessions are designed to be followed on a weekly or two-weekly basis. These time indications may vary among users. Besides the sessions, the participants have several resources at their disposal: a homework station, extra information, reading tips, useful links, and addresses for additional help. Patients randomized to the usual care arm will receive care as it is standardly offered to ICD patients in the three centers, comprised of an information booklet about ICD treatment, standard clinical follow-up visits, and home monitoring of the device (if applicable).

**Table 2 T2:** Components of the 12-week web-based intervention

*Components*	*Topics dealt with*
**▪ Psycho-education about the ICD**	▪ Emotional reactions to ICD therapy
**▪ Problem-solving skills**	▪ Which aspects of ICD therapy may lead to distress
**▪ Cognitive restructuring**	▪ How to deal with shocks
	▪ Disease-specific issues and fears
**▪ Relaxation training**	▪ How to prevent the avoidance of activities
**▪ Personalized feedback by a therapist via the computer**	▪ Interpretation of bodily symptoms
	▪ How to cope with uncertainty
	▪ Help-seeking behaviour
	▪ How to cope with stress

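### Utilization and cost-effectiveness are primary endpoints, yet all observed resource use after randomization rests on one TiC-P form at week 52, with no stated recall window

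*Protocol article*

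**What the plan says.** The Study endpoints section of the protocol article lists among the primary endpoints "health care utilization; and (i_iii_) cost-effectiveness of the intervention". The Methods part of the abstract states that "All primary endpoints will be assessed with standardized and validated disease-specific or generic questionnaires", and the section on assessment of primary endpoints refers to Table 1 for the measures.

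In Table 1 the row for health care utilization and cost-effectiveness holds one instrument, the "Trimbos/iMTA questionnaire for Costs associated with Psychiatric Illness" (TiC-P), marked at T0 and T3, with T1 and T2 empty. Every other instrument in the table is marked at T1, T2 and T3.

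On timing, the section on procedure, randomization and follow-up says that "patients will be asked to complete the baseline assessment between 5 and 10 days (T_0_) after implantation". Randomization follows once the completed baseline has reached the coordinating center. The same section says that "the follow-up assessments will take place 14 (T_1_), 26 (T_2_), and 52 weeks (T_3_) post implantation". The intervention arm "will receive an internet-based intervention starting 2 weeks after implantation", and the intervention lasts 12 weeks.

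The article gives no recall window for the TiC-P, and names no diary, claims extract or record review for resource use.

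**The concern.** A baseline form completed before randomization can describe only earlier care. It helps with baseline adjustment but holds nothing about what happened under either allocation. That leaves one follow-up form, about 38 weeks after the intervention has ended.

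No choice of recall window removes the difficulty. A short window leaves most of follow-up unobserved and requires extrapolation from the end of the year. A long one asks patients to remember contacts with care over most of a year. The weeks during and just after the intervention, when a change in care use is most plausible, are the furthest from the form.

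Two primary endpoints depend on these data. Incremental cost is one half of any cost-effectiveness result, and utilization is an endpoint in its own right. The schedule also bears on missing data: a patient lost after week 26 can have two follow-up values on the other scales but none on cost.

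**Working it through.** **The blanks in Table 1.** They do not look like a text-extraction fault. The row for the posttraumatic stress scale correctly keeps its empty T0 cell, and the TiC-P row keeps two empty cells between its marks.

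**Inputs from the protocol article.** T0 is at day 5 to 10. T1, T2 and T3 are at weeks 14, 26 and 52. The intervention starts at about week 2 and lasts 12 weeks, so it runs over about weeks 2 to 14. Time after randomization is about 52 − 2 = 50 weeks.

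**Assumption.** The recall window *r* (in weeks) is not in the article, so a range is used.

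**Schedule as written.** Share of weeks 2–52 covered by the T3 form = min(*r*, 50)/50. Share of the intervention period covered = max(0, 14 − max(2, 52 − *r*))/12.

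| *r* (weeks) | Weeks 2–52 covered | Intervention weeks 2–14 covered |
|---|---|---|
| 4 | 4/50 = 8% | 0% |
| 13 | 13/50 = 26% | 0% |
| 26 | 26/50 = 52% | 0% |
| 38 | 38/50 = 76% | 0% (52 − 38 = 14) |
| 39 | 39/50 = 78% | 1/12 = 8% |
| 50 | 50/50 = 100% | 12/12 = 100% |

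Counting from T0 (day 5 to 10) instead of week 2 changes little: about 8%, 25–26% and 51% for windows of 4, 13 and 26 weeks.

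**With T1 and T2 added.** The gaps between forms are about 12 (weeks 2–14), 12 (weeks 14–26) and 26 (weeks 26–52) weeks. Share covered = [min(*r*, 12) + min(*r*, 12) + min(*r*, 26)]/50.

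- *r* = 4: (4 + 4 + 4)/50 = 24%
- *r* = 13: (12 + 12 + 13)/50 = 74%
- *r* = 26: (12 + 12 + 26)/50 = 100%

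If each form asks about the time since the previous one, coverage is 100%. The longest recall is then 26 weeks instead of about 50, which is 26/50 = 52% of the length.

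**Sample size.** The article's figure of 350 is not in question. An effect size of 0.30, two-sided alpha of 0.05 and power of 0.80 reproduce 175 per arm. That calculation concerns anxiety and does not depend on the TiC-P schedule.

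**The case against.** The strongest reply is that the harm turns on a recall window that a journal article may properly leave to the full protocol or a health-economic plan. That the window is unstated is indeed no finding in itself. But the article does state the schedule, and the schedule obliges any window either to omit follow-up time or to be very long.

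Several stronger readings are tempting, and the article does not support them.

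- **Most of the year's costs are missed.** This is true only for windows below about 25 weeks. With 26 to 50 weeks of recall, less than half of the period is missed, although all or part of the intervention period still falls outside any window shorter than 50 weeks.
- **Patients lost before week 52 contribute no cost data.** They have a baseline TiC-P, and the statistical section keeps all randomized patients in the analysis and imputes missing values. What they lack is any observed cost after randomization.
- **The cost of the intervention itself is lost.** Delivery is run by the trial, with automated e-mails and feedback time capped at 60 minutes per participant. It can be costed from trial records. Patients' other care use in weeks 2 to 14 cannot.
- **Recall will bias the comparison in a known direction.** Both arms complete the same form at the same time. The article offers no basis for a direction or size of bias in the difference between arms.

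Two further replies have some force. The article sets no explicit cost horizon, so a one-year total is an inference from the week-52 follow-up. And the week-14 and week-26 packs each already hold 11 questionnaires, with eight saliva samples (four on each of two days) at week 14. A sparse cost schedule may have been a deliberate choice to limit burden.

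**Conclusion.** The point holds as a weakness in a stated design choice. It is neither an arithmetical error nor a contradiction. For two primary endpoints, all observed resource use after randomization comes from one form at week 52.

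The size depends on the assumed recall window: about 8%, 26% and 52% of weeks 2 to 52 at 4, 13 and 26 weeks. The intervention period is not covered at all for any window up to 38 weeks, and full coverage requires about 50 weeks of recall. For patients lost before week 52, follow-up cost would be wholly imputed, with no follow-up cost observation of their own to inform it.

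The conclusion assumes that the intervention runs over about weeks 2 to 14, that costs are wanted over follow-up to week 52, and that no other source of resource-use data exists. The last rests on the article's own statement that all primary endpoints are assessed by questionnaire. A reader should not infer that most costs are certainly lost, or that the powered comparison on anxiety is affected; neither follows.

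**What to change.** In Table 1, mark the TiC-P at T1 and T2 as well as T0 and T3, in both arms. Set the recall period of each follow-up form to the time since the previous assessment (about 12, 12 and 26 weeks), and sum the three intervals to obtain total cost. Take the cost of delivering the intervention from trial records.

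The cost is one more form in each of two packs already sent, at weeks 14 and 26. No new contact is needed. The downside is some added respondent burden on top of 11 questionnaires. No change to the schedule of the Type D scale is needed to offset it.
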